### Sampling Procedure

A randomized, three-staged, stratified, cluster sampling strategy was usedin order to select a representative sample of the general population aged 45 to 75 years of age. The first stage selected 60 census enumeration areas using probability proportional to size, with implicit stratification by socioeconomic level of the enumeration area. The second stage selected 40 households from each enumeration area using systematic sampling. The third stage selected one household member between 45-75 years of age for the study. The final sampling was stratified by gender, with 50% men and 50% women, and age distribution based on recent population census data[13,14](Figure 1).

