## Statistical Analysis

### Sample size

The calculated sample size is 6,000 participants (1,500 per site). This sample will be sufficient to provide precise estimates of the prevalence of COPD by gender and site and associated risk factors, in three age-defined categories: 45 to 54, 55 to 64 and 65 to 75 years old. The proposed sample size is sufficient to comply with the precision requirements of a complex sample that assumes a design effect of 1.5 and the prevalence of risk factors of interest of 5% or greater (Table 2). All power calculations used a statistically significant alpha level of 0.05 and a statistical power of 85%, which will permit detection of moderate and large relative risks.

**Table 2 T2:** Sample size for a highly complex study design for effect and design of specific proportion

Proportion	Design Effect				
	1.0	1.5	2.0	2.5	3.0

0.26-0.50	30	45	60	75	90

0.25	32	48	64	80	96

0.20	40	60	80	100	120

0.15	53	80	107	133	160

0.10	80	120	160	200	240

0.05	160	240	320	400	480

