### Statistical Analysis

General characteristics of the population will be described. For continuous variables, mean and median, range, standard deviation, and/or quartile range will be calculated according to the distribution of each variable. In the case of categorical variables, absolute and relative frequencies will be calculated.

In order to determine the prevalence and incidence of COPD and patient characteristics and risk factors, the design effect of the first stage unit of sampling will be considered. Weighting will be based on the relation between the number of individuals included in the study and the population size and composition of each site according to the most recent census data. Likewise, the analysis will be carried out by socioeconomic strata, gender and age categories.

To assess the association between risk factors and COPD, linear regression and simple and multiple logistical regressions will be used according to the nature of the response variables. Continuous variables that are not normally distributed will be evaluated by the application of transformations and categorizations wherever applicable[25]. The secular trends in risk factors over time will be evaluated with methods of statistical analysis that take into account the correlation between repeated measures. To evaluate the changes in risk factors over time by sub-groups of interest, generalized estimation equations will be used. To estimate the rate of accumulated COPD incidents, the Kaplan-Meir method will be used. The log rank test will be used to compare the differences between the curves of accumulated incidence events. The log rank test of trend will be applied to analyze the relationship between the accumulated risk by quartile group or by created groups of interest. In order to quantify the relationship between risk factors and the incidence of COPD, the Cox Proportional Hazards method will be used. Potential confounders and interactions will be explored.

Appropriate diagnostics will be carried out to test goodness of fit, co-linearity, and atypical observations in each model. In all cases, fulfillment of assumptions in the model by means of exploration of residual behavior will be verified. Statistical analysis software STATA 10.0 and SAS 9.0 will be used[26,27].

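### The log-rank and log-rank trend tests named for COPD incidence cannot, in standard form, carry the design effect and census weights promised in the same section

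*Protocol article*

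**What the plan says.** The Sampling Procedure section describes a three-stage cluster sample. Sixty enumeration areas are drawn "with implicit stratification by socioeconomic level of the enumeration area", then 40 households per area, then one person per household. The Sample size section plans for "precision requirements of a complex sample that assumes a design effect of 1.5 and the prevalence of risk factors of interest of 5% or greater".

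The Statistical Analysis section makes a general commitment covering prevalence, incidence and risk factors: "the design effect of the first stage unit of sampling will be considered". It adds weights based on census size and composition, and says that results will be analysed by socioeconomic stratum, gender and age.

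For incidence it names Kaplan-Meier curves and two tests. The first is: "The log rank test will be used to compare the differences between the curves of accumulated incidence events". The second is: "The log rank test of trend will be applied to analyze the relationship between the accumulated risk by quartile group or by created groups of" (last word of the sentence omitted). Cox regression is also named, to quantify risk factors for incidence. No weighted or clustered form is attached to any of these. Incidence is secondary at follow-up; the primary follow-up outcome is change in lung function.

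**The concern.** The variance of the standard log-rank statistic treats each person at risk as an independent draw with equal weight. That suits a simple random sample. Here people are sampled within enumeration areas and analysed with census weights, and the standard test has no term for either. An analyst who runs the named tests does not carry out the section's own general commitment.

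The error depends on how far the comparison groups follow areas. Socioeconomic stratum is the clearest candidate, if it is defined at area level as in the sampling plan. Biomass exposure may be another. For such groups, incidence differences that are only variation between neighbourhoods could be reported as risk-factor effects. They could also disagree with a design-based prevalence analysis of the same factor.

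**Working it through.** **Inputs from the protocol article**
- Alpha 0.05 (Sample size section, given for power calculations; sidedness not stated, two-sided assumed).
- Design effect 1.5 (Sample size section, for precision of proportions).
- 1,500 people per site; 60 areas; 40 households per area; one person per household.

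**Reproducing the plan's figure.** Table 2 follows n = (8/p) x D, with 30 x D for proportions of 0.26-0.50. At p = 0.05 and D = 1.5, 8/0.05 x 1.5 = 240, as printed. All other cells reproduce too.

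**Cluster size.** 60 x 40 = 2,400 households cannot supply 6,000 people at one per household, so 60 areas is read as per site. Then m = 1,500/60 = 25 per area. If the whole design effect is due to clustering, the intra-area correlation of the outcome is (1.5 - 1)/(25 - 1) = 0.0208.

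**Actual size of an unadjusted 5% test.** If the true variance is D times the assumed one, the size is P(chi-square_k > critical value / D).
- 1 df (two groups, or trend): 2 x (1 - Phi(1.96/sqrt(1.5))) = 0.1095, or 0.1095/0.05 = 2.2 times nominal.
- 3 df (four groups): P(chi-square_3 > 7.815/1.5) = 0.157.

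**Fewer people at risk.** If a fraction f of each area's 25 is at risk and followed (assumed), D = 1 + (25f - 1) x 0.0208.

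| f | D | 1-df size |
|---|---|---|
| 0.9 | 1.45 | 0.103 |
| 0.8 | 1.40 | 0.097 |
| 0.7 | 1.34 | 0.091 |

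**Groups only partly patterned by area.** With intra-area correlation rho_x for the grouping variable, D = 1 + 24 x rho_x x 0.0208 = 1 + 0.5 rho_x.

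| rho_x | D | 1-df size |
|---|---|---|
| 0 | 1.00 | 0.050 |
| 0.1 | 1.05 | 0.056 |
| 0.2 | 1.10 | 0.062 |
| 0.5 | 1.25 | 0.080 |
| 1 | 1.50 | 0.1095 |

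**Simulation** (assumed 8% four-year incidence, beta-binomial between areas, no group effect, unadjusted tests). One site, 60 areas of 25, 4,000 replicates:
- Groups constant within areas: 0.102 (two groups), 0.110 (trend), 0.156 (3 df).
- Groups assigned person by person: 0.044-0.047.

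**Does the remedy hold its size?** In a second simulation (3,000 replicates, area-level groups), the ordinary trend test rejected 10.9% with 240 areas and 9.9% with 60. The same test with variance clustered on area rejected 5.2% and 4.5%. The simulations model clustering only; they do not test the weighting.

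**The case against.** The strongest reply is that the commitment to the first-stage design effect and weights names incidence and risk factors and comes before the list of methods, so it governs all of them. Logistic and Cox regression are also named without a weighted or clustered form, and nobody would conclude from this that they will be run naively. A journal article may leave such mechanics to fuller documents.

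There are also limits on size. The trend-test groups are not said to be area-level. Income, education, tobacco and biomass exposure are collected from individuals. The socioeconomic strata of the analysis are not defined as those of the sampling plan. The 1.5 is a planning value for proportions, and weighting can contribute to it as well as clustering. The 0.05 is stated for power calculations. Incidence is secondary.

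Most of this stands as a limit on the size and the wording. It does not remove the mismatch. Regression models take weights and clustered variance without changing their name; the standard log-rank and trend tests have no place for either. Elsewhere the same section does say when correlation is to be handled: for repeated measures, and through generalized estimating equations for subgroup changes. The article chose and named these tests, so the issue is what it fixes, not what it leaves out.

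**Conclusion.** The concern holds in a limited form. The section promises that incidence will be analysed with the sampling design in view, and then names two tests that in standard form cannot do so.

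The size is conditional. About 11% (1 df or trend) and about 16% (3 df) apply if the tests are run unadjusted, the design effect of 1.5 carries over to incidence and is all due to clustering, each area has 25 people at risk, and groups are constant within areas. With 70-90% at risk and followed, the 1-df rate is about 9-10%. Partly area-patterned groups give about 6-8%. Factors that vary independently within areas stay near 5%.

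A reader might infer that the protocol plans an unadjusted analysis, or that its incidence comparisons in general run at twice the nominal error rate. The document supports neither. It states a general commitment to the design effect and weights, gives no design effect for incidence, and does not say that the compared groups follow areas.

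**What to change.** For this secondary outcome, replace the log-rank and log-rank trend tests with a Wald or score test from a census-weighted Cox model with robust variance clustered on enumeration area. Use group indicators for the overall comparison and an ordered score for trend. Keep weighted incidence curves as descriptive plots. If incidence is analysed as a yes/no outcome at year four, apply the same weights and clustering to that model.

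This takes one or two sentences. Cox regression is already planned, and the area identifier and weights are already needed for the prevalence analysis. The small downside is that P values for area-patterned factors become less favourable.

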## Ethical Considerations

The protocol has obtained formal ethical approval from the respective Institutional Review Boards in Argentina, Chile, Uruguay, and USA. The PRISA study will strictly follow guidelines for the protection of the rights of human volunteers. All investigators and personnel in the study have attended a training session regarding this theme, certified by the NIH. All participants will sign the informed consent during the initial visit. To protect participant confidentiality, the information included in database will not contain personal information. Each participant in the study will be assigned a unique identification code (ID), which will not be a mathematical derivation of the medical registration of the patient or any other personal identifier.

All transmission of data obtained in the field, along with the central lab results and the coordination of the data will take place via a secure website requiring a password for access. Blood samples will be stickered with the ID only, to be transmitted and processed in the central lab. No personal information of any type will be in any presentation or publication. In addition, all study personnel will sign a confidentiality agreement to not divulge information or data related to the study.

## Discussion

Despite the burden of COPD in Latin America, there is limited knowledge of the prevalence and incidence of COPD, patient characteristics and provider prescribing regimens in this region. Although the PRISA study is not representative of the total population in Latin American, it is, to our knowledge, the first population-based cohort study addressing knowledge gaps and informing public health policy-making on the impact of COPD in Argentina, Chile and Uruguay.

The close cooperation between experienced researchers in Argentina, Chile, Uruguay, and Tulane University in the USA is a study strength. Methodology to estimate prevalence is similar to that used in the PLATINO study, which will allow comparison of data between the Latin American countries studied in the PLATINO study and the baseline phase of the PRISA study. The PRISA study, however, has the advantage of being the first longitudinal study of pulmonary function in Latin America. In addition, questionnaires used in the HCHS/SOL study[19], a cohort study performed on Hispanic population in the USA will be also used in the PRISA study, allowing additional comparison between PRISA study subjects and the Latin American and Hispanic communities in the United States.

It is clear that chronic pulmonary diseases, including COPD, are leading causes of morbidity and mortality worldwide. Our study will provide important information about the epidemiology of COPD in select cities in Argentina, Chile and Uruguay. In the first phase of the study, it will describe COPD prevalence and associated risk factors, socioeconomic status, concurrent medical history, patient characteristics and physician prescribing trends. In the second phase, it will describe the decline in lung function over time, COPD incidence and any changes in patient characteristics and physician prescribing trends. This information is paramount to the development of appropriate public health legislation and preventive interventions.
